## Abstract

**Background:**

Recent research has suggested that interventions at the workplace might be the most potent ingredient in return to work interventions, but few studies have investigated the different effects of workplace interventions as part of occupational rehabilitation programs. The comprehensive design described in this article includes effect (on return to work and health outcomes), and health economic evaluations of a workplace intervention added to a multicomponent rehabilitation program. Qualitative and mixed method studies will investigate sick-listed persons’, rehabilitation therapists’ and employers’ perspectives on the usability and outcomes of the rehabilitation program and the workplace intervention. The program and intervention are provided to patients with musculoskeletal, psychological or general and unspecified diagnoses. The program is multi-component and includes Acceptance and Commitment Therapy, physical exercise, patient education and creating a plan for increased work participation.

**Methods:**

Persons who are employed, aged from 18 to 60 years, with a current sick leave status of 50% or more and a diagnosis within the musculoskeletal, psychological or general and unspecified chapters of International Classification of Primary Care-2 (ICPC-2) will be recruited to a researcher-blinded parallel-group randomized controlled trial. All participants take part in an in-patient occupational rehabilitation program, while the intervention group also takes part in an intervention at the workplace. The effect and economic evaluation will investigate the effect of the added workplace intervention. The primary outcome measures will be time until full sustainable return to work and total number of sickness absence days in the 12 months after inclusion. Health economic evaluations will investigate the cost-effectiveness and cost-utility. Qualitative studies will investigate rehabilitation therapists’ experiences with working towards return to work within an ACT-approach and stakeholders’ experiences with the workplace intervention. A mixed methods study will combine quantitative and qualitative findings on the participants’ expectations and motivation for return to work.

**Discussion:**

The outline of this comprehensive study could represent an important addition to the standard designs of return to work evaluation. The mixed methods design, with qualitative approaches as well as a rigorous randomized controlled trial, might prove useful to shed light on contextual factors.

**Trial registration:**

ClinicalTrials.gov: NCT02541890. September 4, 2015.

## Background

Work disability is considered one of the biggest challenges for governments and policy makers in The organisation for economic co-operation and development (OECD) countries [1]. In Norway, sickness absence rates are the highest in the OECD area [2], with costs of disability benefits totaling to approximately 4–5% of GDP in 2010 [1]. Hence, many European countries, including Norway, have implemented legislation and acts to prevent long-term absence and work disability due to health problems [3], and many rehabilitation programs have been established to help patients return to work (RTW) [3–9]. In Norway, inpatient occupational rehabilitation programs are widespread. They usually consist of group-based and individual cognitive behavioral- and physical exercise sessions, as well as patient education [10–12], but have rarely included workplace interventions [13]. Individuals are usually referred to such programs by their general practitioner, but can also be referred from the Welfare and Labor Service.

So far, most occupational rehabilitation programs have been tailored for specific diagnosis groups, most often for musculoskeletal disorders [7, 14–17] and some for mental health problems [18–21]. Several of these programs have shown effect on return to work and other outcomes [7, 14]. Different models have been used to help understand work disability; the medical model, the biopsychosocial model, and the case management ecological model, where the environmental influence has gradually become more important. Now, political, economic, cultural and work place environment are considered to interact with the persons own behavior and attitudes [22]. Thus, sickness absence is no longer solely attributed to the person’s health problems, but is considered a result of complex interactions between the person’s physical and behavioral characteristics and the socio-cultural environment, including the health services, the work environment and the system providing financial compensation [22, 23]. Together with an increased focus on the high level of co-morbidity among sick-listed persons [24–27], these developments warrant more generic programs in order to be useful for patients with different and overlapping diagnoses. The effect of generic programs are still unclear. In addition, many have argued that interventions to prevent work disability and long-term sickness-absence should address all stakeholders and systems involved in this field [28, 29]. Employers have a key role in the return to work process [1] that seems to be confirmed in systematic literature reviews [30–32]. Similarly, the need for collaboration between different types of health care professionals in managing and preventing disability has also been highlighted in the literature [16, 22, 33]. Collaboration and coordination between the different actors is thus needed to prevent prolonged sickness absence and to improve return to work [22, 34].

Workplace interventions are defined as initiatives linked to the workplace, including adaptations at work or involvement of the work-environment stakeholders. A landmark study from Canada suggested that interventions at the workplace might be the most potent ingredient in occupational rehabilitation, especially when combined with a clinical intervention [16]. The study was later partly replicated in the Netherlands and Denmark [7, 35, 36]. In a Dutch study Lambeek et al. [7] found that a workplace intervention as part of a clinical rehabilitation program was more effective in facilitating return to work than usual care. However, the effects of specific intervention components are uncertain and publication bias is present [37]. Several systematic reviews have reported that, for patients with back pain, and to some extent for patients with mental disorders, multimodal rehabilitation which includes interventions at the workplace is more effective than other interventions [30–32, 38]. However, the effect of workplace interventions on sustainable return to work is so far unclear [32]. It seems important to involve the different actors, such as patient and employer, in active consultation and consensus about how to modify the work environment, specific work tasks or the work organization to facilitate return to work [38, 39], and this collaborative approach is recommended [29].

Hence, current knowledge points towards more multimodal and generic occupational rehabilitation programs that comprise the different stakeholders in the return to work process, including the workplace. There is thus a need for effect studies which can attend to the complexity of multimodal interventions, as well as more heterogeneous patient groups. In addition to randomized controlled designs to investigate effects on return to work, qualitative methodological approaches should focus on the experiences of the different stakeholders in the return to work process (sick listed persons, service providers, and employers), and help uncover any unknown facilitators and barriers in the return to work process. Qualitative methodological approaches could also investigate the stakeholders’ perceptions of usability and other potential outcomes from initiatives to support work participation and return to work. It is also necessary to assess the cost-benefit of such interventions through economic evaluations.

## Objectives

The objective of this article is to describe the protocol of a study which endeavors to encompass all the requirements described above. The proposed study design includes an effect evaluation (a randomized controlled trial), an economic evaluation, two qualitative studies and one mixed methods study which combines qualitative and quantitative data. The proposed study design is presented in Fig. 1.

**Fig. 1 Fig1:**
[figure not shown]
Study design

The development of this study and the study design is based on the experiences from a large randomized controlled trial (RCT) conducted in Central Norway [11, 12, 40]. Interviews with rehabilitation therapists and participants made it clear that very few participants had been in contact with the workplace or employer during the rehabilitation program. A qualitative study also showed that the participants, at the end of the program, perceived return to work as a long and complex process, and few of them felt ready to return to work [41]. To enhance the return to work focus and improve the return to work rates, the researchers, in collaboration with the clinic, developed and piloted an intervention at the participants’ workplace. This, added to the rehabilitation program, is proposed as the intervention in the RCT.

Based on the findings of high comorbidity in sick-listed persons, and to encompass the largest group of sick-listed persons in Norway, the rehabilitation programs and the workplace intervention are developed specifically for a heterogeneous patient group; patients with a diagnosis within the musculoskeletal, psychological or general and unspecified chapters of International Classification of Primary Care-2 (ICPC-2). Large part of the program’s psychological therapy is provided in groups where persons with different diagnoses are mixed. This is still a rather new approach in occupational rehabilitation. The therapists' educational backgrounds are also heterogeneous, including backgrounds such as nurses, physiotherapists, psychologists, and social workers. All were provided training and supervision in the same psychological therapy approach. Acceptance and Commitment Therapy (ACT) [42, 43] is chosen as the psychological therapy approach. The ACT approach has, so far, very limited use in occupational therapy [40, 44, 45].

### The Norwegian sickness absence system

All legal residents in Norway are included in the Norwegian public insurance system. Medically certified sick leave is compensated with 100% coverage for the first 12 months. The medical certificate can, and is encouraged if possible, to be graded from 20% to 100%, independent of employment fraction. This means that if you are employed in 50% position and are 50% on sick leave, you are working 25%. After 12 months of sick leave, it is possible to apply for long-term medical benefits, compensating approximately 66% of the income.

## Methods

The aims of the studies are to:Through a randomized controlled trial, investigate whether an occupational rehabilitation program with a workplace intervention can improve sustainable return to work and reduce sickness absence, compared to an occupational rehabilitation program without a workplace intervention.Through an economic evaluation, assess whether an occupational rehabilitation program with a workplace intervention is cost effective, compared to a program without a workplace intervention.Through two qualitative studies and one mixed methods study, investigate the patients, rehabilitation therapists, and employers’ experiences of the usability and perceived outcomes of the programs and the intervention.

### Participants and recruitment

People living in Trøndelag (two counties in Central Norway) are eligible for inclusion if they 1) are aged 18 to 60 years, 2) are sick-listed 2–12 months, 3) hold at least a 20% job position (e.g. minimum one day per week), 4) have an employer, 5) have a sick-leave status of at least 50% off work, 6) anticipate at least four more weeks of sick-leave, and 7) have a diagnosis within the musculoskeletal, psychological or general and unspecified chapters of ICPC-2. The participants’ diagnoses are as assessed by the participants’ general practitioner (GP). In addition, potential participants must currently have an employer. Exclusion criteria are: Being self-employed, having or being under consideration for a serious somatic or mental health/substance abuse disorder (assessed by the screening clinic), currently undergoing rehabilitation, having significant problems with working in a group (assessed by the screening clinic based on questionnaires and clinical interview), insufficient comprehension of Norwegian language to participate in group sessions and to fill out questionnaires, scheduled for surgery within the next 6 months, or being pregnant.

#### Sample size

Sample size is calculated in line with the requirements in the randomized controlled trial. Comparison of return to work with Kaplan Meier survival analysis with log rank test with a hazard ratio of 0.6 (alpha 0.05, beta 0.20) would require 63 participants in each group. As we use register-based sickness absence data, there will be no loss to follow-up in the intention-to-treat analyses of primary outcomes. However, to provide greater statistical power for questionnaire-based outcomes we will include at least 80 participants in each group. The sample size estimation was based on results from previous studies in this field [7, 16, 36], as well as preliminary results from ongoing studies [11].

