### Data collection

#### Effect evaluation

Data on sickness benefits and other social benefits will be based on register data from the National Welfare Administration. Self-reported data will be collected by internet based questionnaires (www.checkware.com) before screening, before the rehabilitation program starts, right after the rehabilitation program has ended, and 4, 8 and 12 months after the end of the rehabilitation program. Participants are invited by text messages to access the website and answer the questionnaires.

*Primary outcomes*
Time from inclusion (i.e. after outpatient screening) until full sustainable return to work (i.e. for at least four weeks without relapse), obtained by national registers.Total number of sickness absence days during 12 months of follow-up from inclusion, obtained by national registers.

*Secondary outcomes*
Readiness, beliefs and motivation for return to work (RRTW) [54].Expectations regarding future work participation and sick leave:

*How long do you think you will be on sick leave from today?* (Less than 2 months; 3–6 months; 7–12 months; more than 12 months; I am currently not on sick leave).

*Given your current health situation, do you think you will be receiving full sick-leave benefits six months from now?* (Yes; no).

*Given your current health situation, do you think you will be receiving graded sick leave benefits six months from now?* (Yes, less than 50%; yes, 50% or more).

(The questions were developed during workshops with the research group.)Work adjustments and consideration from employer and colleagues:

*Has your employer adjusted your work situation according to your health complaints (*e.g. *changes in work tasks, working hours or facilities)?* (Yes; no; I do not need adjustments).

*To which extent do you feel that your*
*employer*
*show consideration for your level of functioning?* (Very much; to some extent; not much; I do not need special consideration).

*To which extent do you feel that your*
*colleagues*
*show consideration for your level of functioning?* (Very much; to some extent; not much; I do not need special consideration)Job satisfaction:

*How do you like your work?* (Not at all; not so much; good; very much).Return to work self-efficacy (RTWSE-19) [55].Health-related quality of life by 15D (15 dimensions) [56].Perceived general health:

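### The 63 per group in the sample size is an event count presented as participants; whether the planned 160 give 80% power depends on a return-to-work proportion of about 75–79% that is not stated

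*Protocol article*

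**What the plan says.** The Sample size section of the protocol article sizes the trial on the comparison of return to work and states that a "log rank test with a hazard ratio of 0.6 (alpha 0.05, beta 0.20) would require 63 participants in each group". It does not say whether alpha is one- or two-sided, and it gives neither a number of events nor an expected proportion returning. It attributes the estimate to earlier studies in the field and preliminary results of ongoing ones.

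It then adds that, because sickness absence comes from registers, "there will be no loss to follow-up in the intention-to-treat analyses of primary outcomes". Enrolment is raised for a different reason: "to provide greater statistical power for questionnaire-based outcomes we will include at least 80 participants in each group".

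The event is defined under Data collection, Effect evaluation, as time from inclusion "until full sustainable return to work (i.e. for at least four weeks without relapse"). The abstract names the primary outcomes as "time until full sustainable return to work and total number of sickness absence days in the 12 months after inclusion". In the list of primary outcomes and in the research questions, the 12-month window is attached only to the sickness absence days.

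**The concern.** The power of a log-rank test is governed by the number of events, not by the number of people randomised. A person who has not fully returned to work by the end of follow-up is censored and supplies no event, however complete the register is. A participant requirement therefore needs an event requirement divided by an expected event proportion. Here the participant figure coincides with the event requirement itself, as if that proportion were 100%.

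Two things are at stake. First, a reader is told that 63 per group is enough for the first primary outcome and that the step to 80 is a bonus for the questionnaires. If the event proportion is well below 100%, some or all of that step is already needed for the primary outcome. Second, a non-significant result would be read against 80% power at a hazard ratio of 0.6, which the stated calculation does not establish.

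**Working it through.** **Inputs.** From the Sample size section: hazard ratio 0.6, alpha 0.05, beta 0.20, 63 per group (126 in total) stated as required, at least 80 per group (160 in total) planned. Equal allocation is implied by the equal group sizes. Assumed here because not stated: two-sided alpha, so (1.960 + 0.8416)² = 7.849.

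**1. Reproducing the stated figure.**
- Freedman: events = ((1 + 0.6)/(1 − 0.6))² × 7.849 = 16 × 7.849 = 125.6, so 126 events, or 63 per group. This is an exact match with no event proportion applied.
- Schoenfeld: events = 4 × 7.849/(ln 0.6)² = 120.3, so 121 events.

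**2. What 63 per group needs.** Share of 126 people who must have the event: 126/126 = 100% (Freedman) or 121/126 = 96% (Schoenfeld).

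**3. Is there another route to 63?** With a one-sided alpha of 0.05 the requirement is 99 events (Freedman) or 95 (Schoenfeld). Then 126 participants would be right if 99/126 = 79% or 95/126 = 75% returned. The article states neither a one-sided test nor such a proportion.

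**4. What the planned 160 need.** 126/160 = 79% (Freedman) or 120.3/160 = 75% (Schoenfeld) returning during follow-up.

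**5. Power over a range of return proportions.** The article gives no proportion, so a range is shown. Further assumptions: censoring at 12 months, constant hazards, and the intervention group returning faster, with control-to-intervention hazard ratio 0.6. If the control proportion returning is p, the intervention proportion is 1 − (1 − p)^(1/0.6), and the expected events d are the total number of people times the mean of the two proportions.
- Power (Schoenfeld) = Φ(½√d × 0.5108 − 1.960)
- Power (Freedman) = Φ(√d × 0.4/1.6 − 1.960)

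| Control return | Intervention return | Overall | Power, 126 people | Events, 160 people | Power, 160 people |
|---|---|---|---|---|---|
| 40% | 57% | 49% | 50–52% | 78 | 60–62% |
| 50% | 69% | 59% | 58–60% | 95 | 68–70% |
| 60% | 78% | 69% | 65–66% | 111 | 75–77% |
| 70% | 87% | 78% | 70–72% | 125 | 80–82% |

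Each power range runs from Freedman to Schoenfeld. A log-rank simulation (exponential times, censoring at 12 months, 6000 runs per setting) gave 60, 70, 77 and 83% for 80 per group, within about two points of the formulas.

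**6. Hazard ratio detectable with 80% power, 160 people.** By Schoenfeld, exp(−2 × 2.8016/√d): 0.53, 0.56, 0.59 and 0.61 for the four rows.

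**The case against.** The strongest reply is that the trial will not enrol 63 per group. The same paragraph commits to at least 80 per group, and 160 people give 80% power once about 75–79% return. The last row of the table meets the target. A reader might infer from the mislabelled figure that the trial fails to deliver its stated power. The document does not support that: it gives no return proportion, so a shortfall at 160 is possible but not demonstrated. This part of the objection stands.

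Three further points limit the claim.
- It is tempting to say that the authors assumed every participant would return. The exact Freedman match makes this the likeliest explanation, but it is an inference. Sidedness is not stated, and a one-sided test with about 75–79% returning would also give 63.
- It is tempting to treat 12 months as the censoring time. The abstract can be read that way, but elsewhere the window belongs only to sickness absence days. Longer register follow-up for the time-to-event outcome would yield more events, so the 12-month horizon in the table is an assumption.
- The register sentence is correct as far as it goes: it is a sound reason not to add a dropout allowance, and it makes no claim about censoring. Nor is the absence of a return proportion a fault by itself in an article that condenses a fuller protocol. It matters here because the participant figure cannot be justified without one.

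The second primary outcome, sickness absence days compared by the Mann–Whitney U-test, does not depend on the event count and is untouched.

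None of this rescues the statement itself. With the usual two-sided alpha, the article's own inputs give events, and it calls them participants.

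**Conclusion.** Wrong as written. With two-sided alpha, a log-rank test at hazard ratio 0.6 and 80% power needs about 126 events (121 by Schoenfeld). The claim that 63 participants per group suffice holds only if 96–100% of them reach full return sustained for four weeks. At the planned minimum of 80 per group, 80% power is not shown rather than disproved: it requires about 75–79% of the 160 to return during follow-up.

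The requirement in events rests only on two-sided testing and equal allocation. The power range for 160, roughly 60% to 82% for control return between 40% and 70%, rests in addition on 12-month censoring, constant hazards and the chosen range of return, none of which the article fixes.

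**What to change.** In the Sample size section:

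1. Replace the requirement of 63 participants per group by one of about 126 return-to-work events in total, and say that alpha is two-sided. If a one-sided test was in fact used, say so and give the return proportion that leads to 63.
2. State the follow-up horizon for the time-to-event outcome and the proportion expected to reach full sustainable return within it, with its source.
3. Restate the power at hazard ratio 0.6, and the detectable hazard ratio, for 80 per group at that proportion. Make clear how far the increase from 63 to 80 serves the primary outcome as well as the questionnaires.

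The register sentence can stay, with a short addition that people not fully back at work at the end of follow-up are censored.

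The cost is rewording one paragraph. No extra participants are needed. The stated power may become less favourable.
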